### The Interventions

The study involved four intervention conditions comprising the two intervention programs presented singly and in combination and an attention-control website administered over a 12 week period. Although a module could not be accessed until the week scheduled for its delivery, it remained open for the remainder of the 12 week intervention period and for 12 months from the commencement of the intervention. Participants in the attention control condition were provided with access to the ITP after the 6-month follow-up assessment. The ITP, ISG and IAC conditions employed the e-couch, WellBeing Board and HealthWatch websites respectively. The weekly content of each intervention websites is summarised in Table 3 and described in detail below.

**Table 3 T3:** Summary of the WellBeing Trial topics for the intervention and control conditions.

	Condition		
	
Week	ITP: e-couch	ISG: WellBeing Board	IAC (Control): HealthWatch
1	Depression: What is depression? Risks & causes	How do you feel? (*Your WellBeing category*)	Environment *(Questions)* Environmental Health *(Information)*
2	Treatments: What works for depression	What helps? Who helps? (*Feeling Better category*)	Nutrition *(Questions)* Nutrition Myths *(Information)*
3	CBT: Thinking about thinking. (identifying thinking patterns that can lead to depression)	General chit-chat (*General category*)	Physical & Mental Activities *(Questions)* Maintaining a Healthy Heart *(Information)*
4	CBT: Changing your thinking (changing your thoughts to change your mood)	Do they understand? (*Your WellBeing forum*)	Physical Health *(Questions)* Energize Yourself (& Your Family) *(Information)*
5	CBT: Changing your behaviour (how to change your mood by doing things differently)	Positive things that happened to you today. (*Feeling Better forum*)	Social & Family Relationships *(Questions)* Medicines in the Home *(Information)*
6	CBT review (work on your workbook)	Jokes (*General forum*)	Travel *(Questions)* Temperature Extremes *(Information)*
7	IPT: Role disputes and relationships	Causes and triggers (*Your WellBeing forum*)	Education & Post Education *(Questions)* Oral Health *(Information)*
8	IPT: Role changes and grief	Your views on antidepressants & Connecting with others (*Feeling Better forum*)	Career & Work Relationships *(Questions)* Blood Pressure & Cholesterol *(Information)*
9	Physical activity (Part 1)	Creative corner (*General forum*)	Music & The Arts *(Questions)* Stroke *(Information)*
10	Physical activity (Part 2)	Effects of stress and feeling bad (*Your WellBeing forum*)	Popular Culture & Movies *(Qs)* Bacteria & Foodborne Illness *(Information)*
11	How to relax	Psychological therapy & improving your self-esteem (*Feeling Better forum*)	Humour *(Questions)* Calcium *(Information)*
12	Review	Alternative and lifestyle approaches (*Feeling Better forum*)	Sport *(Questions)* Back Pain *(Information)*

#### ITP: E-couch (depression stream)

This automated online psychological intervention is a research version of the depression stream of the online application e-couch http://ecouch.anu.edu.au. The intervention comprised a depression literacy module together with five interactive self help tools designed to reduce depressive symptoms.

The depression literacy module contained information about the symptoms and types of depression and their diagnosis, sources of help, information about the prevalence and disability burden associated with depression, depression risk factors, and evidence-based medical, psychological and lifestyle treatments for depression based on updated systematic reviews and clinical practice guidelines. The self help module comprised online versions of treatments amendable to delivery online and known to be effective in face-to-face therapy, bibliotherapy or computerised or Internet delivery. These included: (a) cognitive behaviour therapy; (b) interpersonal therapy; (c) applied relaxation; and (d) physical activity. An example page from the research version of e-couch is illustrated in Figure 1.

**Figure 1 F1:**
[figure not shown]
**Screenshot from the e-couch program week 7**.

#### ISG: WellBeing Board

The WellBeing Board is a research ISG which uses a bulletin board format to facilitate discussions. It was developed for the trial based on the primary author's experience in running a public ISG and a thematic analysis of a randomly selected subset of topics on that board. The WellBeing board was divided into three main categories: Your Wellbeing, Feeling Better and General. Each week one, or in the case of weeks 8 and 11, two new forums or topics were introduced for each category in turn (see Table 3).

Participants were instructed to login to the website at least twice a week, read any new messages that had been posted, and contribute a minimum of four posts/messages a week. They were also encouraged to login to the WellBeing Board website as often as they wished, to introduce additional topics for discussion and to continue discussions across weeks.

A detailed list of the WellBeing board rules appeared when the participant first registered on the board and was available at all times on the Board home page and in the participant's manual. Discussion of suicide, self harm and other traumatic topics was not permitted. Participants were requested to use pseudonyms and to refrain from posting any material that might identify them. Links and email addresses were filtered out of posts and signatures using an automated script.

The Board was moderated by a member of the WellBeing trial staff who enforced the rules but did not participate in the board discussion. The entry page of the WellBeing Board is illustrated in Figure 2.

**Figure 2 F2:**
[figure not shown]
**Screenshot of the entry page for the WellBeing Board**.

#### ISG + ITP: WellBeing Board plus e-couch

The combined intervention involved the delivery of both e-couch and a dedicated WellBeing Board each week over the 12 week intervention period. The trial protocol including reminders was identical to that for the individual conditions. To prevent contamination across conditions separate ISGs were used for the combined intervention and ISG-only conditions. The combined condition ISG also differed from the single ISG intervention condition in that it incorporated an additional forum designed for participants to discuss their experiences on e-couch.

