Age 18 to 65 years	Self-reported current or imminent treatment from a mental health professional or mutual support group at the time of recruitment.

Kessler Psychological distress (K10) score > 22	Current treatment with Cognitive Behaviour Therapy.

Home or work access to the Internet	Self-reported current or past experience with or diagnosis of psychosis, schizophrenia or bipolar disorder.

Consent to participate	Current or prior participation in another project conducted by the lead investigator's research centre.

Eligible individuals who agreed on the telephone to participate in the project were randomised (see below) to one of the four trial conditions and were sent an information sheet about the project and the intervention conditions together with a consent form. At this point, however, neither they, their interviewer nor the project coordinator were informed of their randomisation status. Randomisation prior to consent and completion of the pre-intervention was undertaken for pragmatic reasons as the trial required the participants in the internet support groups to commence simultaneously. Undertaking stratified randomisation post-consent and post-baseline survey would have either introduced a significant delay between screening and baseline measures and the commencement of the intervention or reduced the available pool of participants.

Those participants who returned consent forms were sent a letter informing them of the condition to which they had been randomised together with a 14 or 15 page user guide containing a week by week overview of their intervention, a 'Frequently Asked Questions' section and a 'Technical Tips' page.

Recruitment to the WellBeing Study was conducted in three waves (Pilot, Wave 1, Wave 2) between August 2008 and May 2009. A subsample of 7000 surveys (randomly selected from the two metropolitan divisions of Canberra and Maribyrnong and the two rural divisions of Murray and Indi) were employed to pilot the survey and protocol. After the successful completion of the intervention phase of the pilot, a further 28,000 surveys were sent to residents in the above divisions. Since these screening surveys did not yield the target sample size for the study, a further 35,000 surveys were sent to the divisions of Bennelong, Higgins, Murray and Riverina.

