### Planned data analysis and sample size

The WellBeing trial aimed to recruit and randomise 500 participants to four conditions (125 per group). The primary analysis will be undertaken on an intent-to-treat basis. Mixed-model repeated measures (MMRM) analyses will be used because this method has been demonstrated to be superior to using the last observation carried forward method for handling missing data in longitudinal designs [52]. For analyses of categorical outcomes, non-linear mixed modelling methods will be used. Based on previous studies, [8] we estimated pre-post effect sizes for the automated training program, the attention placebo and the ISG to be .6, .1, and .35 respectively. Power was set at 80% and calculations conservatively assumed a correlation of .5 between pre- and post-test measurements. Under these conditions the target sample size could detect a change from baseline of approximately .25 standard deviations in *a priori *contrasts of treatment arms conducted within the framework of omnibus test of condition by time mixed model repeated measures analysis. It is planned that the unique effect of the combined treatments will be tested by appropriate contrasts. It is possible that the combinations of treatment (e-couch and ISG) will prove no better than the individual programs. Conversely, cumulative effects or potentiation (synergy) may be observed. The target sample size ensured that the study is powered to detect an effect of .25 in either direction.

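### Support-group members interact on shared boards, but the planned analysis and the .25 SD power figure make no visible allowance for correlation within a board

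*Protocol article*

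**What the plan says.** Under ISG: WellBeing Board, the intervention is a bulletin board on which members are told to read one another's messages and to post several times a week. Under ISG + ITP: WellBeing Board plus e-couch: "To prevent contamination across conditions separate ISGs were used for the combined intervention and ISG-only conditions". Under Participant recruitment, randomisation before consent is explained by the fact that "the trial required the participants in the internet support groups to commence simultaneously", and recruitment ran in three waves (7,000, 28,000 and 35,000 surveys). The e-couch and HealthWatch programs are used individually.

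Under Planned data analysis and sample size: "Mixed-model repeated measures (MMRM) analyses will be used because" of its handling of missing data. Treatment comparisons are "contrasts of treatment arms conducted within the framework of omnibus test of condition by time mixed model repeated measures analysis". The planning inputs are 125 participants per arm, "Power was set at 80% and calculations conservatively assumed a correlation of .5 between pre- and post-test measurements", and "we estimated pre-post effect sizes for the automated training program, the attention placebo and the ISG to be .6, .1, and .35 respectively". The conclusion is that "the target sample size could detect a change from baseline of approximately .25 standard deviations". The section names no correlation other than the one between a person's own pre- and post-test scores. The number of boards is not stated anywhere.

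**The concern.** In the ISG-only and combined arms, part of the intervention is the other members. People on the same board share its tone, its active contributors and its discussions, so their outcomes can be correlated. The separation of the two arms' boards shows that the investigators expected members to influence one another. The other two arms have no such grouping, so any clustering is one-sided (partially nested).

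The primary objectives compare ISG with control, the active arms with each other, and the combination with each component. Of the six pairwise contrasts, four set an arm with boards against one without, one (ISG v combined) has boards on both sides, and only ITP v IAC has none. If board correlation exists and is ignored, intervals for five of the six are too narrow as statements about support groups in general. One unusually lively or unhelpful board could then be reported as an effect of depression support groups as a class.

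**Working it through.** **Step 1: reproduce the plan's figure.** With r = .5, the SD of change is sqrt(2 × (1 − .5)) = 1.0 baseline SD. Alpha is not stated, so two-sided .05 is assumed. The detectable difference is (1.960 + 0.842) × SD × sqrt(1/n1 + 1/n2).
- 250 v 250 (a factor margin in Table 1): 2.802 × sqrt(2/250) = 0.2506. Power at .25 is 79.8%.
- Pre-post change within one arm of 125: 2.802 / sqrt(125) = 0.2506.

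Both match the stated .25, and both assume full independence between participants. The figure therefore contains no allowance for shared boards. (One arm against another, 125 v 125, gives 0.354 on change scores even under independence. That is a separate matter, not pursued here.)

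**Step 2: assumptions for clustering.** The ICC and board count are not in the documents. Two layouts are taken, both with three boards per arm (one per wave):
- equal boards: m = 125/3 = 41.7;
- boards in proportion to surveys sent (10%, 40%, 50%): size-weighted m = 125 × (.1² + .4² + .5²) = 52.5.

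**Step 3: formulas.** DEFF = 1 + (m − 1) × ICC, applied to ISG arms only. The ratio of true to independent SE is sqrt((DEFF + 1)/2) for an ISG arm v a non-ISG arm, and sqrt(DEFF) for ISG v combined. Real error of a nominal 5% test = 2 × [1 − Φ(1.96/ratio)]. Power at .25 for 250 v 250 = Φ(.25/sqrt((DEFF + 1)/250) − 1.96). Example, equal boards at ICC .02: DEFF = 1 + 40.7 × .02 = 1.81; ratio = sqrt(2.81/2) = 1.19; error = 9.8%.

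**Step 4: results, three equal boards per arm.**

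| ICC | DEFF | SE ratio, ISG v non-ISG | Error | SE ratio, ISG v combined | Error | Power at .25, 250 v 250 |
|---|---|---|---|---|---|---|
| .005 | 1.20 | 1.05 | 6.2% | 1.10 | 7.4% | 76% |
| .01 | 1.41 | 1.10 | 7.4% | 1.19 | 9.8% | 72% |
| .02 | 1.81 | 1.19 | 9.8% | 1.35 | 14.6% | 65% |
| .05 | 3.03 | 1.42 | 16.8% | 1.74 | 26.0% | 50% |

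**Step 5: results, unequal boards (m = 52.5).**

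| ICC | DEFF | Error, ISG v non-ISG | Error, ISG v combined |
|---|---|---|---|
| .005 | 1.26 | 6.5% | 8.0% |
| .01 | 1.52 | 8.0% | 11.1% |
| .02 | 2.03 | 11.1% | 16.9% |
| .05 | 3.58 | 19.5% | 30.0% |

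**Step 6: one board per arm.** With m = 125, DEFF is 2.24 at ICC .01 and 7.20 at ICC .05, so the SE ratio for ISG v non-ISG would be 1.27 and 2.03. In this layout the board effect is fully confounded with the arm, and no model can separate them.

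The null behind these error rates is a zero average effect over boards in general. The calculations use normal quantiles and treat the ICC as known.

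**The case against.** The strongest counter-argument has four parts.

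- *The article does not say that members are modelled as independent.* It gives no random effects or covariance structure, and a board term could sit in an analysis plan that is not shown. This stands: a reader might infer that the model ignores boards, but the documents do not establish it. It does not dispose of the power statement, which is in the article and does rest on independence. Nor would a routine board term settle the matter, since a board variance is poorly estimated from two or three boards per arm and not identifiable from one.
- *The size is unknown.* This also stands. At ICC .005 the ISG v IAC error is only about 6.5% with the unequal boards. The Background section expects substantial dropout from unguided online programs, and members who rarely visit the board could dilute any correlation.
- *Participants were randomised individually.* Board correlation therefore arises after randomisation, through the boards themselves. If a support group affected nobody, this source would not inflate ISG v IAC. A reader might take the error rates above as plain false-positive rates under no effect at all, and that reading is not supported. They apply when boards do differ in effect but average to zero.
- *Inflating standard errors and limiting inference to the boards studied pull in opposite directions.* That is fair if both are attached to the same interval. It is resolved by giving each interval its own interpretation.

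**Conclusion.** The point holds in conditional form. The documents show interacting groups nested in two of the four arms, an analysis description with no visible allowance for them, and a power figure that reproduces only under independence. For any positive board ICC, precision is overstated for every contrast with an ISG arm when the aim is to speak about support groups in general.

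Over the two three-board layouts and ICCs from .005 to .05, the real error of a nominal 5% test runs from about 6% to 20% for ISG v non-ISG and from about 7% to 30% for ISG v combined. With equal boards, power at .25 lies between about 76% and 50%. These ranges rest on an assumed board count and assumed ICCs. The documents do not support saying that every ISG standard error is wrong by a known amount.

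**What to change.** 1. Keep the MMRM as the primary analysis.
2. State how many boards each ISG arm had and how many members each board had.
3. For every contrast involving an ISG arm, add a sensitivity table, fixed before the outcomes are analysed, with variance inflated in the ISG arms only at ICC 0, .005, .01, .02 and .05. Present it as a range. The documents give no basis for choosing one ICC as a pass/fail threshold.
4. Say that the .25 SD power claim holds only under independence, and give the values under stated board assumptions (for three equal boards per arm, about 72%, 65% and 50% at ICC .01, .02 and .05).
5. State that the unadjusted MMRM result applies to the boards studied, and that the inflated intervals indicate the uncertainty in generalising to other support groups. If there was one board per arm, say that board and arm cannot be separated.

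A fixed wave effect may be useful for other reasons, but it does not deal with correlation within a board.

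The cost is a few lines of text and one table, with no new data and no design change. The downside is wider intervals for the ISG contrasts and a less favourable stated power.

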#### IAC: HealthWatch

In the absence of a suitable existing web-based attention control condition, the HealthWatch website was purpose built for the WellBeing trial. It comprised 12 modules, each consisting of two online components.

The first component involved a series of online questions probing factors potentially related to depression and wellbeing. This component was modified and extended to 12 modules from a previously reported 5 module telephone control condition [9,15,33]. For example, the introduction to the humour topic (Week 11) commenced with the explanation: "Some people believe that humour and laughter can prevent depression and increase the enjoyment of life. Today we would like to ask you to think about humour and whether it is important to your mood". This introduction was followed by a series of 16 multiple choice and open-ended questions: e.g., Do you enjoy telling jokes? (Responses: Yes, No, I can never remember any); How often do you tell jokes (Responses: Never, Rarely, About once a month, at least once a week, Most days); What is the funniest joke you can remember? (Open ended response); Overall do you think your moods are affected by humour?

The second component of the each weekly website module contained online information about a series of 12 topics related to wellbeing. The content in this component of the modules was adapted for Australian use from publications of the National Institute of Health and other US government sources which permit public use. Material was chosen which addressed topics relevant to wellbeing but which contained no or minimal information about interventions for depression or stress.

Participants were instructed to log onto the website each week to respond to the questions in first component of the module, and then to read the material in the second. An example page from HealthWatch website is shown in Figure 3.

**Figure 3 F3:**
[figure not shown]
**Screenshot of a page from week 3 of the HealthWatch website**.

### Intervention Study Procedure

All participants who provided written consent were sent a user ID and password by automated email. A second automated email sent one week prior to the commencement of the intervention directed them to log onto the website to complete the online baseline survey.

Each of the four conditions was then delivered over a period of 12 weeks. Participants received a weekly automated email informing them when the next module of their program was available. Those who failed to log onto the module were sent an email reminder four days after the initial email. Those who failed to log in thereafter received a telephone reminder from their interviewer. The current week's module was only available after first completing the modules assigned in the preceding week or weeks.

At the end of the 12-week trial, an automatic email was sent to participants requesting that they complete the post-intervention survey. Reminders were sent according to the protocol employed at baseline. Further follow up using this protocol was undertaken at 6 months and 12 months after the commencement of the intervention. The flow of participants is shown in Figure 4.

**Figure 4 F4:**
[figure not shown]
**Participant flow through the study**.

Participants could withdraw from the study without explanation at any stage by informing the Trial Manager or their interviewer via email or telephone.

### Randomization and allocation concealment

#### Allocation concealment

As required by ICH guideline E9 [34], randomisation was carried out by the trial biostatistician who was not involved in the day-to-day conduct of the trial.

#### Randomisation sequence

Potential participants were randomised using a stratified block design with stratification by level of psychological distress (high/low distress level on K10), gender (male, female, uncommitted), and location of residence (metropolitan/rural). Randomization schemes with a fixed block size of four were generated for each strata using the web site Randomization.com http://www.randomization.com.

### Measures

Table 4 provides a summary of measures taken at each assessment point.

**Table 4 T4:** Measures employed in the screening and baseline, post intervention and follow-up phases of the WellBeing Study

	Screening	Baseline	Post-test	6 month	12 month
Depressive symptoms (CES-D)		X	X	X	X

Anxiety symptoms (PSWQ)		X	X	X	X

Quality of Life		X	X	X	X

Disability		X	X	X	X

Self-esteem		X	X	X	X

Perceived social support		X	X	X	X

Loneliness		X	X	X	X

Depression knowledge		X	X	X	X

Stigma	X	X	X	X	X

Help-seeking behaviours		X	X	X	X

Empowerment		X	X	X	X

User perceived utility of the Internet		X	X	X	X

Satisfaction & user perceived benefits/negative effects of intervention			X	X	X

Participation in healthcare			X		

Sociodemographics	X				

Psychological distress (K10)	X				

User perceived mental health status	X				

Depression & general anxiety symptoms (DASS-21)	X				

Social anxiety screening (BSPS)	X				

Panic screening	X				

Information needs	X				

Intervention group preference	X				

